## Sample size calculation

The impact of total aortic arch repair compared to more limited aortic resection on the early and late outcomes will be one of the main topics of research from this registry. Therefore, in the light of the expected limited frequency of this surgical strategy, we performed a sample size analysis considering the extent of distal aortic resection. Despite the limitation of a pooled analysis which did not take in to account the cumulative incidences from competing risk analysis and the segment of repeat operation, Poon et al. [23] estimated a pooled hazard ratio on 0.73 (95%CI 0.56–1.18) of freedom from any late aortic reoperation for total arch replacement. Based on this hazard ratio, a sample size of 163 patients per study groups would be enough to reject the null hypothesis (alpha 0.05, power 0.80). Pan et al. [24] reported a freedom from distal reoperation after ascending aortic resection at 8 years of 95.3% which was not statistically different from that of hemiarch or total aortic arch repair (92.4%, *p* = 0.22). For the sample size calculation of a non-inferiority trial, we assumed a freedom rate from distal aortic reoperation of 95% and we considered that a difference in the reoperation rate as large as 10% in favor of a total aortic arch repair still allow the less extensive repair to be non-inferior (delta = 0.1, power 0.90, one-sided confidence 97.5%), the required sample size would be 100 patients per each group. We assume that about 5% of patients have undergone total arch repair in this collaborative registry and therefore a study population of 4000 patients would be enough to investigate the impact of total aortic arch repair in preventing late aortic reoperation in patients with acute TAAD. The participating hospitals are expected to provide a sample size of more than 6000 patients (i.e. at least a mean of > 20 procedures for acute TAAD each year), which would prevent a type II error.

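### The 10-point non-inferiority margin is twice the assumed 5% reoperation rate, so the 100 per group derived from it does not support the claim that 4000 patients are enough

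*Protocol article*

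**What the plan says.** The Sample size calculation section of the Protocol article names total arch repair against more limited resection as a main research topic and gives two calculations. The first is a superiority calculation from a pooled hazard ratio of 0.73 (163 per group).

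The second is a non-inferiority calculation:

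- Assumed rate: "we assumed a freedom rate from distal aortic reoperation of 95" per cent. One rate is given, with no statement of which repair it belongs to.
- Margin: "we considered that a difference in the reoperation rate as large as 10% in favor of a total aortic arch repair still allow". What is allowed is a conclusion that limited repair is non-inferior.
- Settings and result: "delta = 0.1, power 0.90, one-sided confidence 97.5%), the required sample size would be 100 patients per each group".

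The rate follows a cited study that "reported a freedom from distal reoperation after ascending aortic resection at 8 years of 95.3" per cent. The section describes this figure as "not statistically different from that of hemiarch or total aortic arch repair (92.4" per cent), with a p-value of 0.22. No reason is given for choosing 10 points.

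The section then assumes that about 5% of patients had total arch repair and concludes that 4000 patients suffice to study whether it prevents late aortic reoperation. More than 6000 are expected.

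**The concern.** A non-inferiority margin should be smaller than the loss that would make the less extensive repair unacceptable for durability. Here it is 10 points on an outcome assumed to occur in 5% of patients. A criterion that wide can be met when limited repair triples the reoperation rate, or when total arch repair removes reoperation altogether.

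Reoperation on the aorta is one of the registry's primary outcomes, and the Discussion expects conclusive results on surgical strategies. A finding of non-inferiority under this margin would carry almost no information on durability. The small sample size that follows from the wide margin also makes the registry look comfortably large for the question.

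**Working it through.** **Inputs (all from the Sample size calculation section).** Freedom from distal reoperation 95%, so reoperation p = 0.05; margin 0.10; power 0.90 (z = 1.2816); one-sided 97.5% (z = 1.9600); total arch share 5%; registry 4000 said to be enough, more than 6000 expected.

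**1. Reproducing the plan's figure.**
n per group = (1.9600 + 1.2816)² × 2 × 0.95 × 0.05 / 0.10² = 10.507 × 0.095 / 0.01 = 99.8, rounded up to 100. The arithmetic is right. It shows that 95% was used in both groups and that the margin is absolute. Relative readings do not give 100: 10% of 95% (9.5 points) gives 10.507 × 0.095 / 0.095² = 110.6, and 10% of 5% (0.5 points) gives about 39,900.

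**2. What the margin tolerates.**
- If 5% is the total arch rate, limited repair may reach 5% + 10% = 15%, three times the rate. As a hazard ratio under proportional hazards: ln(0.85)/ln(0.95) = 3.17.
- If 5% is the limited-repair rate, total arch repair can lower it by at most 5 points (5% to 0%). Margin / largest possible benefit = 10/5 = 2.
- The cited rates give the same picture. Reoperation was 100 − 95.3 = 4.7% and 100 − 92.4 = 7.6%, both below 10%.

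**3. Chance of declaring non-inferiority when total arch repair prevents every reoperation.** True rates are 5% (limited) and 0% (total arch). Limited repair is declared non-inferior when the upper 97.5% limit of the difference is below 10 points. The last two columns are exact binomial enumeration.

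| Per group | Wald limit if exactly 5% v 0% is observed | P(non-inferior), Wald | P(non-inferior), Newcombe |
|---|---|---|---|
| 100 | 9.3% | 62% | 44% |
| 200 | 8.0% | 87% | 70% |
| 300 | 7.5% | 95% | 88% |

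Example for the first row: 0.05 + 1.96 × √(0.05 × 0.95/100) = 0.05 + 0.0427 = 0.0927. The 200 and 300 per group correspond to 5% of 4000 and 5% of 6000. For the unmatched 3800 v 200 the probability is about 100% with either limit.

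**4. What a narrower margin needs (same formula, 1:1).**
- 5 points, equal to the whole assumed rate: 400 per group; 400/0.05 = 8000 registry patients.
- 4 points: 624 per group; 624/0.05 = 12,480 registry patients.

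**5. Smallest margin the registry supports at 90% power.** Margin = 3.2415 × √(0.0475 × (1/n1 + 1/n2)).

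| Groups | Margin |
|---|---|
| 200 v 200 | 7.1 points |
| 300 v 300 | 5.8 points |
| 200 v 3800 | 5.1 points |
| 300 v 5700 | 4.2 points |

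The last two rows are best cases because they ignore weighting. With an assumed variance inflation of 1.5 to 2.0, 4.2 points becomes about 5.1 to 5.9 points (4.185 × √1.5 and × √2).

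**6. Expected precision of an estimate.** 95% CI half-width = 1.96 × √(0.0475 × (1/n1 + 1/n2)): 3.1 points for 200 v 3800, 2.5 for 300 v 5700, 4.3 for 200 v 200, 3.5 for 300 v 300. These are also unweighted.

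**The case against.** The strongest reply is that the margin has little force in this plan. The Statistical analysis section schedules Kaplan-Meier, Cox and competing-risk analyses with hazard ratios and 95% CIs, and no non-inferiority test. The margin appears only in the sample size paragraph, and in a retrospective registry no recruitment or allocation depends on it. This stands. A reader might infer that the plan will formally declare non-inferiority, or declare limited repair non-inferior and total arch repair superior from the same data. The documents schedule no such declaration. What remains is the use of the criterion to justify the sample size.

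Three other inferences go too far:

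- That limited repair is certain to be called non-inferior even if total arch repair abolishes reoperation. It is likely, not certain: 62% (Wald) or 44% (Newcombe) at 100 per group. The 0% scenario is also a limiting case; the calculation itself uses 95% in both groups.
- That 4000 rests on the 100. At a 5% share, 100 per group needs 100/0.05 = 2000 patients and 163 needs 163/0.05 = 3260, so the superiority figure is the larger. The 100 is still offered as support.
- That the margin can be expressed as a multiple of the effect in the superiority calculation. The hazard ratio of 0.73 is for any late aortic reoperation and the 95% is for distal reoperation, so a ratio would mix endpoints.

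It can also be said that margin size is partly a clinical judgement, and the Background does describe a trade-off between early operative risk and late reoperation. That could motivate a generous margin. It does not explain 10 points, and it cannot make a margin of twice the event rate informative about durability.

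**Conclusion.** The point holds. The article fixes an absolute margin of 10 points on an assumed 5% event rate and gives no reason for it. Depending on which repair the 5% describes, the criterion either tolerates a tripling of reoperation (15% v 5%, hazard ratio about 3.2) or is twice the greatest benefit total arch repair could have. The 100 per group is arithmetically correct but does not support the statement that 4000 patients are enough to study prevention of late reoperation.

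The probabilities assume simple proportions with complete follow-up and independent groups, and they depend on the interval method. The comparison of 10 points with 5% depends on none of these. The 163 per group in the same section is a separate matter and is not assessed here.

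**What to change.** Remove the non-inferiority criterion and its 100 per group from the Sample size calculation section. In its place, state that the difference between repairs in cumulative incidence of distal reoperation, with death as a competing event, will be reported with its 95% CI. Give the precision expected from about 200 to 300 total arch patients, noting that weighting and incomplete follow-up will widen it. This fits the competing-risk analysis already planned.

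If a non-inferiority claim is kept:

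- justify on clinical grounds a margin clearly below the 5% event rate, and say which repair the 5% describes;
- restate the required number (400 per group at 5 points and 624 at 4 points, 1:1);
- state that about 300 total arch patients support at best about 4.2 points on the unweighted full cohort or 5.8 points with 1:1 matching, and only wider margins after weighting, so the registry may not support the claim.

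The cost is wording and a less favourable sample size justification. No new patients are needed if the non-inferiority claim is dropped. If it is kept with 1:1 groups, even 5 points implies about 8000 registry patients at a 5% share, against the more than 6000 expected.

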## Statistical analysis

Statistical analyses will be conducted using Stata v. 15.1 (StataCorp LLC, Texas, USA) and SPSS v. 27.0 (IBM Corporation, Armonk, NY, USA) statistical softwares. Continuous variables and outcomes will be reported as mean and standard deviation as well as median and interquartile range. Categorical variables and outcomes will be reported as counts and percentages. A *p* < 0.05 will be set for statistical significance. Differences between the study groups will be evaluated using the Fisher’s exact test, the Chi-square test, the linear-by-linear association test, the Mann-Whitney test and the Kruskall-Wallis test. The McNemar test and paired samples T-test will be used in the paired groups. Propensity score matching will be performed to balance treatment strategies for baseline differences. A propensity score will be estimated using a non-parsimonious multilevel mixed-effects logistic regression considering the cluster effect of the participating centers whose results may be affected by the referral pathway, surgical techniques and perioperative care. Multilevel mixed-effects logistic regression model will include all available baseline variables. The estimated propensity score will be employed for inverse propensity score weighting analysis and one-to-one propensity score matching analysis using a caliper width of 0.1 to 0.2 of the standard deviation of the estimated logit. Standardized differences < 0.10 will be considered an acceptable imbalance between the matched cohorts.

Survival analysis will be performed using the Kaplan-Meier method with the log-rank test and the Cox proportional hazards method. Competing risk analysis with the Gray’s test will be performed for late non-fatal adverse events because patient’s death might hinder the observation of these events. Regression models will include covariates with *p* < 0.05 or *p* < 0.2 in univariate analysis according to the number of covariates of interest. Risk estimates will reported as hazard ratios and subdistribution hazard ratios with their 95% confidence intervals.

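### The non-inferiority sample size (100 per group, 90% power) has no matching analysis: the article plans only difference tests and hazard ratios, with no rule using the margin

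*Protocol article*

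**What the plan says.** The Sample size calculation section names total arch repair against more limited resection as one of the registry's main topics and gives two separate calculations for it.

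- **Difference.** A hazard ratio of 0.73 for late aortic reoperation, alpha 0.05 and power 0.80, giving 163 per group.
- **Non-inferiority.** "For the sample size calculation of a non-inferiority trial, we assumed a freedom rate from distal aortic reoperation of 95"%. The largest tolerated loss is "a difference in the reoperation rate as large as 10% in favor of a total aortic arch repair", which would "still allow the less extensive repair to be non-inferior (delta = 0.1, power 0.90, one-sided confidence 97.5"%), and "the required sample size would be 100 patients per each group".

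The section then assumes that about 5% of patients had total arch repair and concludes that 4000 patients would suffice. More than 6000 are expected.

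The Statistical analysis section sets the rule p "< 0.05 will be set for statistical significance. Differences between the study groups will be evaluated using the Fisher’s exact test" and other tests of difference. For reoperation, the relevant sentence is "Competing risk analysis with the Gray’s test will be performed for late non-fatal adverse events". Effects are reported as hazard ratios and subdistribution hazard ratios with 95% confidence intervals. The section contains no non-inferiority hypothesis, margin, one-sided level, risk difference or decision rule.

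**The concern.** A power statement is a property of a particular test. The 90% belongs to a test that compares a one-sided 97.5% confidence limit for an absolute difference in reoperation with a margin of 0.10. The tests in the analysis section address a different null hypothesis, that of no difference. Under the calculation's own assumption of equal rates, the expected result of a difference test is non-rejection, and that alone supports no conclusion about non-inferiority.

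At stake is what can be claimed for the less extensive repair. Followed as written, the analysis section gives no rule by which non-inferiority could be declared. The article would still carry a 90% power figure suggesting that the question had been provided for.

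**Working it through.** **Inputs, all from Sample size calculation:** freedom from distal reoperation 0.95, taken as equal in both groups; margin 0.10; one-sided alpha 0.025 (z = 1.960); power 0.90 (z = 1.282); 5% total arch repair; 4000 needed and 6000 expected.

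**1. Reproduce the printed number.** Two proportions, unpooled variance, 1:1:

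n = (1.960 + 1.282)² × 2 × 0.95 × 0.05 / 0.10² = 99.8, so 100 per group.

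Power at 100 per group: the standard error is √(2 × 0.95 × 0.05 / 100) = 0.0308, and Φ(0.10/0.0308 − 1.960) = 90.05%. The printed figures are right for a margin-based test on an absolute difference. Close variants do not give 100: one-sided 0.05 gives 82, and power 0.80 gives 75.

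**2. Apply the planned difference tests under the same assumption.** Exact enumeration of two binomials at 95% and 95%, 100 per group, two-sided 0.05:

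- chi-square rejects in 4.4%;
- Fisher's exact test rejects in 2.1%;
- Gray's test has a nominal level of 5%.

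None of these rejections would be evidence of non-inferiority, and neither would a non-rejection.

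**3. Size of the error if non-significance were read as no worse.** Suppose the less extensive repair is truly 10 points worse (85% v 95%), with complete follow-up. Group sizes: 100 as printed; 5% × 4000 = 200; 5% × 6000 = 300, each matched 1:1. Exact enumeration:

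| Per group | Chi-square power | Fisher power | Non-significant |
|---|---|---|---|
| 100 | 68.3% | 58.6% | 32–41% |
| 200 | 92.8% | 90.5% | 7–10% |
| 300 | 98.8% | 98.3% | 1–2% |

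A non-inferiority test at the stated level would wrongly pass in about 2.5% at the margin, whatever the group size.

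**4. Check the remedy.** If the margin-based test were written into the analysis, the same formula gives 90.05% power at 100 per group and 99.6% at 200, so no extra patients are needed on this ground.

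Steps 1 to 4 treat freedom from reoperation as a simple proportion at one time point, as the article's own calculation does. Censoring and competing death are not modelled, because the inputs for them are not in the document.

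**The case against.** The strongest reply has four parts.

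*The article is condensed.* The sample size section already fixes the endpoint, direction, margin and confidence level, and a statistical analysis plan that is not shown may hold the interval method and decision sentence. This stands only in part. The analysis section is detailed enough to give caliper widths and stepwise entry probabilities, and it names the test and the effect measure for late non-fatal events. Those named methods do not match the non-inferiority design, so two printed sections disagree.

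*The other calculation fits.* This stands. The 163 per group for a hazard ratio of 0.73 is a difference design that suits the Cox and Gray analyses. The 4000 is also justified by a difference question, whether total arch repair prevents late reoperation. A reader might infer that the whole study was powered for a test it will not run, or that its size is wrong. The document supports neither: 200 total-arch patients exceed both 163 and 100.

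*No one says that a non-significant test will be read as non-inferior.* This also stands. A reader might infer that intention, particularly because the cited rates of 95.3% and 92.4% are described as not statistically different, but the article does not state it. The error rates in the working are therefore conditional on a misreading. The figure at 100 per group should not be taken as the study's own, since 200 to 300 total-arch patients are expected. The planned weighted analysis is not limited to 1:1 groups either: an unadjusted comparison of 200 v 3800 has 99.9% power for 95% v 85%.

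*The reported intervals could serve.* A two-sided 95% interval does have the one-sided 97.5% level. Under proportional subdistribution hazards, and taking 95% and 85% as event-free proportions on that scale, the margin translates to a ratio of ln 0.85 / ln 0.95 = 3.17. It would thus be too strong to say that a hazard ratio can never be set against the margin. But the article makes no such translation and gives no rule, and the 90% was not computed on that scale.

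**Conclusion.** The point holds for one of the two calculations. The 100 per group is arithmetically correct, but its 90% power at one-sided 97.5% attaches to no analysis the article describes. Under the assumed equal rates the planned tests reject in about 2–5% of cases, and neither outcome of those tests establishes non-inferiority. The practical risk depends on group size and on a reading that the article does not itself make: with a true 10-point difference and complete follow-up, it falls from 32–41% at 100 per group to 1–2% at 300. The total sample size is not in question on this ground. The correction should be made because it is cheap and settles, before analysis, what may be claimed.

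**What to change.** In the Statistical analysis section, add the analysis that the non-inferiority calculation presupposes:

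- In the matched or weighted cohort, estimate the difference (less extensive minus total arch) in cumulative incidence of distal aortic reoperation, with death as a competing event, at a pre-stated time point. The 8 years of the cited rate is one example.
- Declare non-inferiority only if the upper limit of the two-sided 95% confidence interval lies below the pre-stated absolute margin.
- State that a non-significant Gray's test is not evidence of non-inferiority.

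Alternatively, delete the non-inferiority calculation and its 90% power from the Sample size calculation section and rest the comparison on the difference calculation alone.

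The first option costs a few sentences and one extra estimate from data already being collected, with no additional patients. Its downside is that a merely non-significant result can no longer be presented as equivalence.

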## Statistical analysis

Statistical analyses will be conducted using Stata v. 15.1 (StataCorp LLC, Texas, USA) and SPSS v. 27.0 (IBM Corporation, Armonk, NY, USA) statistical softwares. Continuous variables and outcomes will be reported as mean and standard deviation as well as median and interquartile range. Categorical variables and outcomes will be reported as counts and percentages. A *p* < 0.05 will be set for statistical significance. Differences between the study groups will be evaluated using the Fisher’s exact test, the Chi-square test, the linear-by-linear association test, the Mann-Whitney test and the Kruskall-Wallis test. The McNemar test and paired samples T-test will be used in the paired groups. Propensity score matching will be performed to balance treatment strategies for baseline differences. A propensity score will be estimated using a non-parsimonious multilevel mixed-effects logistic regression considering the cluster effect of the participating centers whose results may be affected by the referral pathway, surgical techniques and perioperative care. Multilevel mixed-effects logistic regression model will include all available baseline variables. The estimated propensity score will be employed for inverse propensity score weighting analysis and one-to-one propensity score matching analysis using a caliper width of 0.1 to 0.2 of the standard deviation of the estimated logit. Standardized differences < 0.10 will be considered an acceptable imbalance between the matched cohorts.

Survival analysis will be performed using the Kaplan-Meier method with the log-rank test and the Cox proportional hazards method. Competing risk analysis with the Gray’s test will be performed for late non-fatal adverse events because patient’s death might hinder the observation of these events. Regression models will include covariates with *p* < 0.05 or *p* < 0.2 in univariate analysis according to the number of covariates of interest. Risk estimates will reported as hazard ratios and subdistribution hazard ratios with their 95% confidence intervals.

Logistic and linear regression analyses will be employed to identify independent risk factors for early adverse events with and without a stepwise approach. For the purpose of developing a risk scoring method from this registry, the study cohort will be randomly divided into two datasets, i.e. the derivation data set (75.0% of patients) and the validation data set (25.0% of patients). Univariate analysis will be performed on all candidate covariates of the derivation dataset to identify predictors of in-hospital mortality. Multiple logistic regression analysis will be then performed using the derivation dataset. A stepwise procedure with a bootstrap approach will be used, and 100 samples will be extracted with a size of 70% of the derivation dataset. A stepwise procedure will be applied to each sample (probability to stay = 0.05; probability to entry = 0.1). Variables selected in at least 50% of the stepwise procedures will be included in the regression model. Additional covariates were selected using a forward selection comparing the Akaike information criterion for the models with and without each covariate. The model with the lowest Akaike information criterion will be selected for each forward step, until the inclusion of a new covariate determined an increase in the Akaike information criterion value. The model will be tested in the validation data set for calibration, using the Hosmer–Lemeshow test, and for discrimination using the receiver-operating characteristic curve analysis. A comparison of the predictive ability of the new score with the current risk scoring methods for prediction of in-hospital mortality will be performed in the overall dataset as well as in the validation dataset using the DeLong test. The improvement of discrimination of the new score will be estimated by calculating the net reclassification index and the integrated discrimination improvement. Finally, to evaluate the adaptability of the new score for prediction of late mortality, Kaplan–Meier curves stratified by deciles of the new score will be plotted.

Interinstitutional and between-surgeons differences in terms of early outcomes will be evaluated using mixed-effects logistic regression. The risk-adjusted rate of adverse binary events at each center will estimated by dividing the observed number of adverse events by the expected number of adverse events, and by multiplying this ratio by the average event rate of the overall series. The expected numbers of adverse events will be calculated with logistic regression. The estimated risk-adjusted rates of adverse events will be summarized as odds ratios and their 95% confidence intervals in caterpillar plots with the x-axis ordered for increasing adjusted rates.

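### In the total arch comparison (about 200–300 matched pairs) some covariates will usually stay at or above a standardized difference of 0.10 by chance, and the paired tests named cannot adjust for them

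*Protocol article*

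**What the plan says.** All of this is in the protocol article.

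- **Propensity model** (Statistical analysis): "Multilevel mixed-effects logistic regression model will include all available baseline variables".
- **Matching** (same section): "one-to-one propensity score matching analysis using a caliper width of 0.1 to 0.2 of the standard deviation of the estimated logit".
- **Balance** (same section): "Standardized differences < 0.10 will be considered an acceptable imbalance between the matched cohorts". The text does not say that this must hold for every covariate, and it attaches no consequence to a miss.
- **Tests for the pairs** (same section): "The McNemar test and paired samples T-test will be used in the paired groups".
- **Other adjusted analyses** (same section): "The estimated propensity score will be employed for inverse propensity score weighting analysis", and "Regression models will include covariates with *p* < 0.05 or *p* < 0.2 in univariate analysis according to the number of covariates of interest". Neither is tied to covariates left unbalanced in the matched cohort.
- **Group sizes** (Sample size calculation): 100 per group for non-inferiority, and for the hazard ratio "a sample size of 163 patients per study groups would be enough to reject the null hypothesis (alpha 0.05, power 0.80)". The share exposed is also given: "We assume that about 5% of patients have undergone total arch repair in this collaborative registry". The registry is said to need 4000 patients and to expect more than 6000.

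**The concern.** Total arch repair against more limited resection is one of the registry's main questions, for early as well as late outcomes, and it is the comparison used for sizing. The exposed group is small, while the propensity model takes in every baseline variable. With so few pairs, sampling variation alone leaves some covariates at or above 0.10 even if the propensity model is correct. The paired tests then compare deaths, or a continuous outcome such as intensive care stay, without using any covariate. If a strong predictor such as malperfusion or urgency class is among those left apart, the matched estimate carries that difference although the data to remove it are in the database.

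**Working it through.** **1. The plan's group sizes.**
- Non-inferiority, 95% free of reoperation in both groups, margin 0.10, one-sided 0.025, power 0.90: n = (1.960 + 1.282)² × 2 × 0.95 × 0.05 / 0.10² ≈ 100 per group, as stated.
- Hazard ratio 0.73, two-sided 0.05, power 0.80: the Schoenfeld formula gives 317 events (158.5 per group) and the Freedman formula 323 (161.5 per group). The stated 163 is close to these only if events are read as patients. That is a separate matter and is not used below.
- Pairs available: 5% × 4000 = 200 and 5% × 6000 = 300, before matching losses.

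**2. Number of covariates.** The document gives no count. Counting items in the section on clinical and operative variables gives about 58 before age and dissection extent, or about 49 with the ten antithrombotic drugs pooled. The fitted model may use fewer, so 15 to 60 were tried.

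**3. Pure-chance benchmark.** With n per group, the SD of one standardized difference is √(2/n): 0.100 at n = 200 and 0.082 at n = 300. One covariate then falls below 0.10 with probability 0.68 or 0.78. This is too pessimistic here, because matching on an estimated score balances better than chance.

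**4. Simulation of the planned matching.** Logistic propensity score, 1:1 greedy matching, caliper 0.2 SD, independent covariates, no centre effect, two strengths of selection, 200 runs per setting for 200 and 300 pairs (fewer for the two largest).

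| Pairs | Covariates | All below 0.10 | Mean number missing | Median largest difference |
|---|---|---|---|---|
| about 200 | 15 | 14–15% | 1.9–2.0 | 0.13 |
| about 200 | 30 | 1–2% | 3.8 | 0.14–0.15 |
| about 200 | 45 | 0% | 5.7–6.1 | 0.16–0.17 |
| about 300 | 15 | 38–50% | 0.8–0.9 | 0.10–0.11 |
| about 300 | 30 | 9–17% | 1.7–2.1 | 0.12–0.13 |
| about 300 | 45 | 4–6% | 2.8–3.1 | 0.13–0.14 |
| about 1180 | 30 | 98% | 0.02 | 0.06 |
| about 2080 | 30 | 100% | 0 | 0.03 |

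A caliper of 0.1 with 30 covariates gave 1% and 16% at 200 and 300 pairs. With 60 covariates, independent or correlated 0.4 within blocks, all passed in 0% and 0.5–3%. Separate runs with 30 to 50 covariates gave about 1.5 to 6 misses and 1–21% all passing over 200 to 300 pairs.

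**5. What this does to in-hospital mortality.** Assumed: 18% mortality (the Nordic 30-day figure in Background), 30 prognostic covariates, no treatment effect, 700 runs per size.

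| Pairs | Mean difference (points) | SD of difference | SD due to covariate imbalance | 95th percentile of its absolute size | McNemar type I error |
|---|---|---|---|---|---|
| about 200 | 0.12 | 3.65 | 1.23 | 2.3 | 3% |
| about 300 | 0.15 | 3.09 | 1.0 | 2.0 | 5% |

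- The simulation error of the mean is 3.65/√700 = 0.14 and 3.09/√700 = 0.12, so neither mean is distinguishable from zero.
- Variance share of imbalance: (1.23/3.65)² = 0.11, and (1.0/3.09)² ≈ 0.10–0.11. This is a ceiling on the gain, since five predictors would not capture all 30. The separate runs put the gain at about 2–6% of the variance. In standard error, √0.98 to √0.89 is a reduction of about 1% to 6%.
- One binary covariate at a standardized difference of 0.15–0.20 (prevalence 10–20%, odds ratio 2–3) shifts mortality by 0.6–1.6 points. The standard error at 200 pairs is √(2 × 0.18 × 0.82/200) = 3.8 points.

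**The case against.** The strongest reply is that nothing here is invalid. Chance imbalance is part of the sampling variation that the test already allows for, and the simulated type I error confirms it. This stands, and it limits the point to conditional error and precision.

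Second, the plan does not rely on matching alone. Inverse weighting, Cox and competing-risk models for late outcomes, and logistic regression for early adverse events are all named, and Limitations speaks of several adjustment methods. This also stands. The paired tests bear only on early outcomes in the matched cohort; the late aortic reoperation used for sizing would not be analysed by McNemar.

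Third, the pairs may be more numerous. The Discussion gives at least 25 procedures per centre per year: 19 × 25 × 16.25 years ≈ 7,700 patients, or about 386 total arch cases at 5%. At about 400 pairs with 30 to 50 covariates, all passed in 24–44% of runs. That softens the point, but a miss remains more likely than not.

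Fourth, a rule for residual imbalance could lie in an analysis plan not shown. That is so, and the lack of such a rule is not the criticism. The criticism is that the article does name the tests for the pairs, and those tests cannot adjust.

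Finally, adjusting for whatever exceeds 0.10 is data-driven, and covariate-adjusted logistic regression changes a marginal odds ratio into a conditional one. Both are right, and the fix has to respect them.

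**Conclusion.** The point holds as a modest improvement. At about 200 to 300 pairs and 30 or more covariates, one or more covariates will usually be at or above 0.10, and the named paired tests leave the resulting prognostic difference in the early-outcome estimates. Its size is an SD of 1.0–1.2 percentage points of mortality, with about 2–11% of the variance recoverable.

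This rests on the 5% total arch share, a covariate count that the document does not state, 18% mortality, and simulations without centre effects. With only 15 covariates and 300 pairs, all pass in 38–50% of runs.

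A reader might infer more, and the document does not support it:
- That the balance rule is bound to fail and discredits the matched analysis. The text never requires the limit for every covariate.
- That the mortality comparison is biased. The leftover differences are chance, with negligible mean error.
- That matching is the main adjusted answer. The text does not rank it above weighting or regression.
- That the whole registry is affected. Treatment comparisons with 1,000 or more pairs meet the limit almost always.

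**What to change.** In Statistical analysis:

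1. State that 0.10 is a diagnostic, reported for each covariate.
2. Replace or supplement McNemar and the paired t-test with a regression in the matched cohort: treatment plus a short set fixed in advance from variables already collected (age, urgency class, malperfusion, lactate, renal function), with standard errors robust to pairing. The set must stay short: at 18% mortality, 200 pairs give about 0.18 × 400 = 72 deaths.
3. For binary outcomes, report a standardized (marginal) risk difference or odds ratio from that model, so that the estimand stays the same.
4. Use the same set in the matched Cox and the weighted analyses, in place of selection by univariate p-value there.
5. Treat adjustment for any further covariate above 0.10 as a sensitivity analysis.

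The cost is a change of wording, slightly more analysis work, and some reliance on the outcome model. No new data are needed.
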